Agencies will be randomly assigned to a study arm using stratified allocation, with a 1:1:1 allocation ratio. Specifically, one-third of the rural agencies will be randomly assigned to each study arm, and separately, one-third of the nonrural agencies will be randomly assigned to each study arm. We will determine rural status using the definition from the US Office of Management and Budget (zip codes within metropolitan areas with an urban core of ≥50,000 people are not rural, and all other areas are rural [44]). In cases where agencies hold *PulsePoint* contracts that cover both rural and nonrural areas, we will assign a status based on the location of the numeric majority of the population in the area. Arm assignment will be according to sequential numbers (from the simple random sample; therefore, this allocation approach is also by definition random) within each stratum (eg, if there are 60 rural agencies, the 20 rural agencies with the lowest random numbers will be assigned to arm 1). This procedure will ensure allocation concealment from the rest of the investigative team until the moment of assignment. Agencies will not be informed that they have been assigned to a specific trial arm; they will simply be contacted using the procedures developed for that arm. Thus, this can be considered a blinded trial.

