#### Establishing Correspondence With Local PulsePoint Decision Makers

Although the PulsePoint Foundation will provide us with a list of participating agencies, its database does not include raw contact details (eg, telephone number and email address), and even these details may not link our study team with the people within the agency who manage the *PulsePoint* system. On the basis of discussions with the PulsePoint Foundation, the following examples describe cases that have occurred in the past:

The point of contact on the agency list may be the accounting or billing representative for the agency, not the person who manages the program, especially among long-term subscribers.The decision makers for the agency may be different now than when the subscription to *PulsePoint* was purchased.

We will need to locate contact information for agencies and verify that the contact details link us with the person who manages the *PulsePoint* subscription, and if not, identify who in the agency does so and how to contact them. In other words, while our trial is intended to study recruitment strategies, we must first ensure that we can access the appropriate individuals at an agency. Once we have identified these points of contact, we can begin recruitment at the agency.

#### Intervention (Recruitment) Arm 1

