##### Approaches

To be replicable at scale, recruitment will be conducted using a combination of video or telephone correspondence (preferably Zoom [Zoom Video Communications, Inc], but telephone where necessary), web links, and emails containing tangible materials. A full recruitment attempt with fidelity to our model will consist of providing emailed materials and web links and attempting between 6 and 10 telephone contacts over approximately 6 months, based on best practice telephone recommendations from the American Association for Public Opinion Research [45]. Recruitment efforts will stop in the event that (1) an agency agrees to participate in the project, (2) an agency asks not to be contacted about the project again, (3) the aforementioned recruitment approaches clearly seem unlikely to yield a change in disposition, or (4) the recruitment timeline ends without the agency making a decision.

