##### Materials

Members of our project staff will develop a short visual presentation to be used as a guideline for videoconference recruitment, along with a parallel set of core written or verbal statements reflecting the content of the presentation in cases where only telephone calls are possible. Drawing lessons from our previous successful agency and organization recruitment experiences [46-49], both the presentation and written statements will cover a limited list of important concepts that need to be imparted (eg, “Participating in this project will require very little time from your agency – we are only asking you to send out one push message each month.”). While moving through these concepts, we will allow conversation to flow freely (eg, semistructured messaging) and also use live documentation of key concepts to ensure message fidelity.

The tangible documentation will consist of digital flyers based on the open-source marketing tools developed by the PulsePoint Foundation for general community agency recruitment, including the use of similar graphical assets and fonts. However, flyers will be differentiated sufficiently from the default *PulsePoint* flyers to make it clear that the organization itself is not conducting this project (eg, we will not use the *PulsePoint* logo). For reference, *PulsePoint*-branded recruitment flyers can be viewed by clicking on the hyperlink provided in the associated reference [50]. As community agencies have already committed to offering standard *PulsePoint* services, we expect that distributing these modified documents to agencies will be a high-leverage recruitment approach. Key messaging will be drawn from local demonstration projects by the study team (eg, “Be a Lifesaver” and “Citizen Opioid Responders”) [51] as well as general marketing and recruitment principles.

As supplemental recruitment content, exemplar videos will be drawn from work produced by the Dearborn County Health Department in Lawrenceburg, Indiana, in collaboration with the study authors to create awareness of this type of initiative and will be included as web links to YouTube versions of the videos [51].

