##### After Recruitment

When communities agree to participate, they will be asked to sign an MOU regarding their participation and to respond to a small set of readiness and implementation items, such as whether the organization is already involved in naloxone distribution and whether there are local laws pertaining to opioid overdose reversal. This information will be used to locally tailor piped text into messages used for H2 (layperson recruitment).

#### Intervention (Recruitment) Arm 2

The recruitment procedures for arm 2 will be similar to those outlined for arm 1. The primary difference will be that the messaging in arm 2 will proactively address several misperceptions or stigmatizing ideas about overdose and naloxone that our recent research has suggested may be prevalent [39]. In particular, content in the fact sheets and scripts for recruitment used in arm 2 will address and preempt the following scientifically unsupported ideas (potentially among others):

“Naloxone causes risk compensation or presents a moral hazard”: it is fairly well established that OEND is not associated with increased opioid use [52-55], nor is it associated with reduced risk perceptions for heroin use [56].“Repeated overdoses are inevitable and people who experience nonfatal overdoses will die of an overdose in the near future”: while individuals who nonfatally overdose are at meaningfully increased risk, especially if they do not matriculate into a cascade of care, the substantive majority will not overdose again in the near future, and even fewer will die of a fatal overdose in the near future [57-60].“Individuals can get high from naloxone”: while this is not possible [6], our study found that 14.2% of our nationally-representative sample still believed this claim [39] to some extent.

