#### Outcome Variables and Measurement

In H1, we hypothesize that more community first responder agencies will agree to participate in the *PulsePoint-OD* program when contacted using procedures in arm 2 (tailored messaging) compared to procedures in arm 1 (standard messaging) within 6 and 12 months of initial contact. Our primary outcome to test this hypothesis will be the number of agencies that agree to participate in the project as a percentage of the number of agencies with which we have been able to identify appropriate points of contact for recruitment. This metric *M* will be computed as follows:

Each agency from the initial PulsePoint Foundation list that is randomized to participate in the study will be given a value *A* that is set at *0*, which indicates that we have not yet identified the appropriate point of contact at the agency.When we have identified a point of contact who can discuss *PulsePoint*, we will set the value for *A* at *1*.To define when a community first responder agency has agreed to participate, each agency will be assigned an ordinal value *R* ranging from *0* to *2*, where *0* will indicate nonparticipation or refusal, *1* will indicate that there is an agreement in principle to participate but that no formal MOU has been established, and *2* will indicate that a formal MOU has been put into place between the agency and the study team. For the purposes of hypothesis testing, we will aggregate values of *1* and *2*, but the data will be documented in ordinal form so that we can identify whether there is a concern with agencies failing to enter the MOU stage after agreeing in principle to participate.Next, the agency recruitment metric *M* for each arm will be the ratio of recruited agencies to total agencies with which active communication has been established: *M*=(*R_R>0_*/*A_A>0_*).

In addition to computation of the primary outcome metric, recruitment activities will be documented in a shared internal database, which will track, at a minimum, the nature, date, and outcome of each instance of correspondence with each community to inform our understanding of the uptake of *PulsePoint-OD* among *PulsePoint* communities and support ongoing mitigation of any issues with recruitment. Using this documentation, we will be able to estimate several secondary descriptive outcomes:

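### The blinded label holds for agencies only: recruiters know the arm, and the H1 outcome values A and R=1 can be scored with the arm known

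*Protocol article*

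**What the plan says.** All references are to the protocol article, Methods, H1: First Responder Agencies.

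- **Label and its basis** (Participants, Eligibility, and Assignment). The article says "Agencies will not be informed that they have been assigned to a specific trial arm" and that they are simply contacted with that arm's procedures. It then concludes "Thus, this can be considered a blinded trial". On the study team it says only "This procedure will ensure allocation concealment from the rest of the investigative team until the moment of assignment".
- **Order of steps** (same section). The random numbers that select the 180 agencies also determine the arm. An agency found on later communication not to be a subscriber is replaced within the same arm.
- **Contact-finding** (Establishing Correspondence With Local PulsePoint Decision Makers). This is a step before recruitment: "we must first ensure that we can access the appropriate individuals at an agency".
- **Delivery** (Approaches; Materials; Intervention (Recruitment) Arm 2). Staff use video, telephone and email. In arm 2, "content in the fact sheets and scripts for recruitment used in arm 2 will address and preempt the following scientifically unsupported ideas". On calls, "we will allow conversation to flow freely (eg, semistructured messaging)". Efforts may end when "the aforementioned recruitment approaches clearly seem unlikely to yield a change in disposition".
- **Outcome** (Outcome Variables and Measurement). Every randomized agency starts at A=0. A becomes 1 "When we have identified a point of contact who can discuss" PulsePoint. R is 0 (refusal or nonparticipation), 1 (agreement in principle, no MOU) or 2 (formal MOU). R=1 and R=2 are pooled for the test, and M is the number of agencies with R>0 divided by the number with A>0.

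**The concern.** An unqualified statement that a trial is blinded invites the reader to assume that delivery and outcome assessment were masked too. Here the people delivering the intervention cannot be masked, and the article describes no masking of those who set the outcome values.

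This matters because M is not a purely mechanical count. Its denominator depends on the team deciding that the right contact has been found. Part of its numerator depends on the team deciding that an agency has agreed in principle. The stated hypothesis is that arm 2 will recruit more agencies than arm 1. If either decision leaned, even slightly, with knowledge of the arm, M would move without any agency behaving differently.

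**Working it through.** **1. Who knows the arm, and when.**

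| Step | What the article fixes | Arm known to staff? |
|---|---|---|
| Sampling and assignment | The statistician's random numbers give sample and arm | Concealed from the rest of the team until assignment |
| Contact-finding, A set | After randomization: A=0 is given to agencies already randomized | Not stated; nothing withholds it |
| Recruitment | Arm-specific scripts and fact sheets | Necessarily yes |
| R set | During or after recruitment | Not stated; no masking described |

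The replacement rule confirms the order: a replacement can go to the same arm after further communication only if the arm was fixed before that communication. Contact-finding precedes recruitment, so A could be settled without knowledge of the arm, but the article does not require it.

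**2. Which parts of M involve judgement.** R=2 is a signed document and largely objective. R=1 has no documentary criterion in the article. A requires deciding that a contact is the appropriate one. The rule for stopping recruitment efforts also leaves discretion.

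**3. The plan's own figure.** For 30% vs 55%, 60 per arm, two-sided α=0.05, the mean proportion is 0.425 and

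power = Φ{[0.25·√60 − 1.96·√(2·0.425·0.575)] / √(0.30·0.70 + 0.55·0.45)} = 0.799.

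The stated 80% reproduces. This point does not change it.

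**4. Numerator illustration.** The assumptions are not from the documents: no true difference, a 40% base rate, A=60 in both arms, and extra R=1 scores in one arm only. The method is exact binomial enumeration of the two-sided pooled z-test, a stand-in for the planned logistic regression without covariates.

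| Extra R=1 among 60 (on average) | Rates compared | Rejection rate |
|---|---|---|
| 0 | 40% vs 40% | 5.1% |
| 3 (3/60 = 5 points) | 40% vs 45% | 8.9% |
| 6 (6/60 = 10 points) | 40% vs 50% | 20.5% |

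With a 30% base rate, suppose a fraction f of non-agreeing arm 2 agencies is scored R=1, so that the arm 2 rate is 0.30 + 0.70f. The rejection rate is 5.2% at f=0, 7.2% at f=0.05 and 13.0% at f=0.10 (rates 30%, 33.5% and 37%).

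**5. Denominator illustration** (counts assumed). With 24 recruited in each arm, M = 24/55 = 43.6% if A=1 for 55 agencies and 24/48 = 50.0% if A=1 for 48. The shift is 6.4 points with no extra agency recruited. Testing 24/55 against 24/48 gives pooled proportion 48/103 = 0.466, standard error 0.0985, z = 0.0636/0.0985 = 0.65 and p = 0.52. On its own this shift distorts the estimate but would not produce a significant result.

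**The case against.** The best case for the plan has five parts.

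- **The label is tied to its basis.** The sentence follows from agency masking and is hedged. Agency masking is described and plausible, and concealment up to assignment is a separate, genuine safeguard. This stands: a reader might infer that the trial has no blinding at all, and the text does not support that.
- **The scorers are not identified.** A reader might infer that the recruiters themselves score A and R. The article uses *we* for A and the passive for R, so this cannot be asserted. Silence on who codes is a detail an article may leave to the full protocol. What remains is that a general claim of blinding is made while A is placed after randomization with nothing to withhold the arm.
- **Recruiters cannot be masked.** This is true, and it is no design error. It is a reason to describe the blinding accurately and to protect the steps that can be protected.
- **Safeguards exist.** A correspondence database records the nature, date and outcome of each contact. R is kept in ordinal form, so R=1 agencies that never reach an MOU can be seen. Key concepts are documented live for message fidelity. These make lenient scoring traceable and the remedy cheap, but they do not mask scoring, and the H1 test still pools R=1 with R=2.
- **The magnitudes are assumed.** This also stands. No miscoding rate is given in the article, and any trial would show similar shifts under the same assumptions.

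**Conclusion.** The concern holds in a limited form. The blinded label is supported for agencies only. Staff delivering the arm-specific scripts are unmasked by necessity, and the article describes no masking of the team that sets A and R. A, the denominator of the primary H1 outcome, is set after randomization and can be set with the arm known. R=1 is a judgement that counts fully as success.

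The documents do not show that bias will occur, that recruiters do the scoring, or that A will in fact be set unmasked. The exposure lies in A, R=1 and the discretion over stopping, not in R=2. The rejection rates of 8.9% and 20.5% are illustrations that depend on a 40% base rate and an average of 3 or 6 one-sided miscodings among 60. They are not estimates for this trial. No sample-size or power figure changes.

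It is still worth acting on. The plan already separates contact-finding from recruitment, so one route for bias in the denominator can be closed by reordering steps, and no recruitment had begun when the protocol was submitted.

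**What to change.** 1. Replace the label with: *Agencies are unaware of allocation; recruiters are not masked.*
2. Have the study statistician hold the arm list and release an agency's arm only after contact-finding is complete and A is recorded. Contact-finding should follow identical steps in all arms.
3. Support each R=1 with a dated written record, such as an email from the agency, in the correspondence database already planned.
4. Add a sensitivity analysis that counts only R=2 as success, with all randomized agencies as the denominator. This removes both A and R=1 from the comparison. It does not remove any effect of unmasked delivery or stopping decisions, which should be acknowledged as a limitation.

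The cost is a wording change, a small logistic step before each arm is released, and one further analysis of data already collected. The team already does the steps involved, and the sample size is unaffected.

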#### Establishing Correspondence With Local PulsePoint Decision Makers

Although the PulsePoint Foundation will provide us with a list of participating agencies, its database does not include raw contact details (eg, telephone number and email address), and even these details may not link our study team with the people within the agency who manage the *PulsePoint* system. On the basis of discussions with the PulsePoint Foundation, the following examples describe cases that have occurred in the past:

The point of contact on the agency list may be the accounting or billing representative for the agency, not the person who manages the program, especially among long-term subscribers.The decision makers for the agency may be different now than when the subscription to *PulsePoint* was purchased.

We will need to locate contact information for agencies and verify that the contact details link us with the person who manages the *PulsePoint* subscription, and if not, identify who in the agency does so and how to contact them. In other words, while our trial is intended to study recruitment strategies, we must first ensure that we can access the appropriate individuals at an agency. Once we have identified these points of contact, we can begin recruitment at the agency.

#### Intervention (Recruitment) Arm 1

##### Overview

The minimum goal of agency recruitment is to reach a memorandum of understanding (MOU) with agencies in which they agree to encourage their layperson *PulsePoint* responders to attend OEND programming and to carry naloxone (arms 1 and 2) and to indicate whether they have done so (arms 1, 2, and 3; Figure 2). The agencies will be asked to accomplish this using push messages prepared by our team and sent out by the agencies; the specific nature of these agency activities is outlined in the *H2: Layperson Responders* section.

**Figure 2 figure2:**
[figure not shown]
Differing agency recruitment procedures for the PulsePoint-OD study by study arm.

##### Development

Our agency recruitment materials will be developed during the first phase of the study and provided in full when the study results are published. Oversight and review of marketing development will be provided by members of the study team and marketing consultants external to the study team. Review of all marketing materials will be granted to the PulsePoint Foundation (a not-for-profit 501[c][3] organization) to ensure consistency with the organization’s branding. As a result of the development timeline, the exact phrases and examples used to illustrate components of the recruitment processes may change between the submission of this paper and the launch of the study.

##### Approaches

To be replicable at scale, recruitment will be conducted using a combination of video or telephone correspondence (preferably Zoom [Zoom Video Communications, Inc], but telephone where necessary), web links, and emails containing tangible materials. A full recruitment attempt with fidelity to our model will consist of providing emailed materials and web links and attempting between 6 and 10 telephone contacts over approximately 6 months, based on best practice telephone recommendations from the American Association for Public Opinion Research [45]. Recruitment efforts will stop in the event that (1) an agency agrees to participate in the project, (2) an agency asks not to be contacted about the project again, (3) the aforementioned recruitment approaches clearly seem unlikely to yield a change in disposition, or (4) the recruitment timeline ends without the agency making a decision.

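### Stop rule (3) lets staff who know the arm end recruitment on judgment before a full attempt is made, so unequal persistence could bias the H1 contrast in either direction

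*Protocol article*

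**What the plan says.** All references are to the Protocol article, Methods.

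- **Effort.** The Approaches section describes a full attempt with fidelity as emailed materials, web links and "attempting between 6 and 10 telephone contacts over approximately 6 months".
- **Stopping.** The next sentence begins "Recruitment efforts will stop in the event that (1) an agency agrees to participate in the project" and lists four alternatives joined by 'or'. Rules (1), (2) and (4) rest on observable facts: agreement, a request for no further contact, and the end of the timeline. Rule (3) applies when "the aforementioned recruitment approaches clearly seem unlikely to yield a change in disposition". It names no number of contacts, no criterion and no decision-maker.
- **Masking.** Participants, Eligibility, and Assignment states "Agencies will not be informed that they have been assigned to a specific trial arm" and on that basis calls the trial blinded. For staff it says only "This procedure will ensure allocation concealment from the rest of the investigative team until the moment of assignment". Under Intervention (Recruitment) Arm 2, "content in the fact sheets and scripts for recruitment used in arm 2 will address and preempt the following scientifically unsupported ideas", so the caller's script differs by arm.
- **Outcome.** Under H1, Outcome Variables and Measurement, M is "the ratio of recruited agencies to total agencies with which active communication has been established". R=0 covers both nonparticipation and refusal. The H1 analysis section treats missing data as already built into M.
- **Records.** Each item of correspondence is logged by nature, date and outcome. The log supports secondary descriptive outcomes, among them the mean number and types of correspondence associated with agreement. The covariates named for H1 are rurality and vote share.

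**The concern.** H1 is meant to isolate message content, so contact effort should be the same in arms 1 and 2. Rule (3) is the one stopping rule that depends on staff opinion. It falls mainly on undecided or unresponsive agencies, where persistence matters most. The protocol describes no masking of recruiters, and someone reading out the arm 2 script cannot be unaware of the arm. The hypothesis is also directional.

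An agency given up after a few calls gets the same R value as one that refused after a full attempt, and the named H1 covariates do not include effort. If staff persist longer in one arm, the contrast mixes message effect with number of attempts. Adjusting for contacts afterwards is a weak remedy, because the number of contacts itself depends on how the agency responds.

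**Working it through.** **The plan's own figure.** Inputs from the H1 sample size section: 60 per arm, 30% vs 55%, two-tailed α=0.05.

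- Pooled proportion 0.425; null SE = √(2×0.425×0.575/60) = 0.0903.
- Alternative SE = √(0.30×0.70/60 + 0.55×0.45/60) = 0.0873.
- Power = Φ[(0.25 − 1.96×0.0903)/0.0873] = Φ(0.837) = 0.799. The stated 80% reproduces.

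**Assumptions for the illustrations (none is in the documents).** All 60 agencies per arm have an identified contact. A full attempt is 8 contacts, the midpoint of 6 to 10. No true difference means 40% in both arms after a full attempt. Rejection rates come from exact enumeration of the uncorrected chi-square test. With equal effort the rate is 0.051.

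**Scenario A: abandoned agencies had average prospects.** Constant chance of agreement per contact: p = 1 − 0.6^(1/8) = 0.062.

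- After 3 contacts: 1 − 0.6^(3/8) = 0.174. After 4: 1 − 0.6^(4/8) = 0.225.
- 25% of one arm capped at 3 contacts: 0.75×0.40 + 0.25×0.174 = 0.344. Gap 5.6 points, rejection 0.098.
- 50% of one arm capped at 3 contacts: 0.50×0.40 + 0.50×0.174 = 0.287. Gap 11.3 points, rejection 0.257.

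**Scenario B: abandoned agencies really were poor prospects.** Assume a remaining chance of only 5% to 10% when effort stops. For comparison, scenario A implies 1 − 0.6^(5/8) = 27% over contacts 4 to 8.

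- 25% of one arm, 5% remaining: loss 0.25×0.05 = 1.25 points; 38.75% vs 40%; rejection 0.053.
- 50% of one arm, 10% remaining: loss 0.50×0.10 = 5 points; 35% vs 40%; rejection 0.087.

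**Hiding a difference.** Take the plan's 30% vs 55%, with 25% to 50% of arm 2 only stopped after 2 to 4 contacts and average prospects. The arm 2 rate is (1−f)×0.55 + f×(1 − 0.45^(k/8)).

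- f=0.25, k=4: 0.495, power 0.60.
- f=0.50, k=2: 0.365, power 0.12.
- Without any contact model, three fewer arm 2 agreements (30/60 instead of 33/60) give power 0.61.

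**Is a floor of six enough?** Under the scenario A model, 6 contacts in one arm and 10 in the other give 1 − 0.6^(6/8) = 31.8% and 1 − 0.6^(10/8) = 47.2%. The rejection rate is 0.41 with no true difference. A floor alone leaves this open.

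**The case against.** Rule (3) refers back to the approaches just described and to a change in disposition, so it can be read as applying once those approaches have been tried and the agency has shown a disposition. It also demands that poor prospects be clear. That reading is possible, but the text does not state it: the four rules are free-standing alternatives. If it was intended, the fix only writes it down.

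Two stronger readings are tempting and are not supported. A reader might infer that the plan sets a six-contact minimum and then breaks it. It does not: six is the lower end of the range that defines a full attempt. A reader might also take 25% or so as the expected false-positive rate. That figure needs half of one arm and none of the other stopped at contact three, and gives stopped agencies average prospects although the rule targets poor ones. Nothing in the documents points to one-sided stopping of that size.

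The contact log would allow a comparison of effort by arm afterwards, the covariate list is left open, and the authors commit to cautious interpretation. This stands as a means of detection. It does not prevent imbalance, and the planned summary concerns contacts that led to agreement, whereas early abandonment would show among agencies that did not agree.

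Finally, call-by-call procedure is often left to a fuller document. Here, however, the article itself states the stopping rule and states it loosely.

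**Conclusion.** The point holds as a risk that the rule permits, with no evidence that it will occur. As written, rule (3) allows staff who know the arm to stop short of a full attempt on judgment, and the result enters M as R=0. The resulting bias could favour either arm. That recruiters know the arm is an inference from the arm-specific scripts and the absence of any described masking.

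The size is unknown. Under the assumed scenarios at 40% and 60 per arm, the false-positive rate lies between about 5% (abandoned agencies truly poor prospects) and about 26% (half of one arm only stopped after three contacts, average prospects). Loss of power for a true difference is equally possible. Because the correction is cheap and data collection had not begun when the protocol was submitted, it should be made before recruitment starts.

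**What to change.** Amend the Approaches section as follows:

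1. Rule (3) applies only after six telephone attempts, the lower end of the plan's own range, have been made and logged, identically in arms 1 and 2.
2. Any explicit decline ends effort at once and is logged as a refusal. Rule (2) now covers only a request for no further contact, so without this change a floor would keep staff calling agencies that had already said no.
3. Both arms use the same target number of contacts within 6 to 10, since the floor alone leaves six versus ten open.
4. Contacts per non-agreeing agency are reported by arm as a fidelity check, separating declines from agencies stopped under rule (3).

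The cost is a few sentences of procedure and some extra calls to unpromising agencies, within the effort already planned. Sample size and the H1 model are unchanged.
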